### Outcomes

This hybrid implementation-effectiveness type 2 pragmatic trial has a mixed methods design. The primary outcomes include: 1) whether patients enrolled in care management programs have been screened for unmet social needs (binary); and 2) whether patients with unmet social needs received a referral to a community organization to address an identified social need (binary). The secondary outcomes include 1) receipt of community services (closed-loop referral) among patients with unmet social needs who were referred to community organizations (binary); and 2) clinical outcomes such as controlled hypertension (among patients with diagnosed hypertension) and controlled diabetes (among patients with diagnosed diabetes). Controlled hypertension is defined as having a blood pressure < 140/90 mmHg at their most recent visit. Controlled diabetes is defined as having hemoglobin A1c ≤ 9.0 percent at their most recent visit. Patients with hypertension and/or diabetes who had a visit but no hemoglobin A1c measurement or blood pressure measurement will be considered to have “uncontrolled” disease.(69) Table 4 outlines how each of the outcomes aligns with the RE-AIM framework.

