Evidence from the implementation of other care management programs(29–33) and health information technologies (HIT)(34, 35) may inform operationalizing the adoption of such enabling technologies. Evidence-based implementation strategies shown to advance the adoption of other technologies in health centers include leadership support,(36) staff training,(37–40) local champions,(41–45) practice facilitation,(46) and audit and feedback.(29–33) Applying these strategies effectively requires consideration of the specific needs and context of different health centers as well as barriers specific to the adoption of enabling technologies to support clinical-community linkages.(29–32, 47, 48) It is critical to engage health center users as partners to guide the development of a set of evidence-based implementation strategies to address such barriers. A structured approach to interactively fine-tuning implementation strategies is needed to develop an implementation support intervention that can then be formally tested to generate evidence for replication across health centers.

This paper describes the protocol for a National Institutes of Health (NIH)-funded study called DEDICATE: Advancing Care Management Adoption in Community Health Centers (R01NR021115). The study will develop and evaluate the effectiveness of implementation strategies designed to support care management teams’ sustained use of EHR-based functionalities that support clinical-community linkages. It will test the hypothesis that health center partners’-adapted implementation strategies applied to enabling technologies will improve the adoption of these technologies and thus social risk screening, community referrals, and receipt of services by patients with unmet social needs. The study’s overarching goal is to improve clinical-community linkages through care management and care coordination programs that serve high-risk patients with complex health and/or social needs.

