## Methods

### Setting

This study will be conducted among health centers that are members of OCHIN, Inc., a multi-state network of community health organizations that serve more than 6 million people in rural and medically underserved communities nationwide. OCHIN is a national nonprofit health IT consultancy that provides a fully hosted and shared EHR platform with tailored tools and expertise, including practice management tools, to > 1,000 care delivery sites across 30 states. While all OCHIN members share a single instance of the Epic EHR, each is an independent organization with its own governing board. Conducting this study in a diverse group of health centers improves the likelihood that its results will be generalizable to other primary care settings, an important feature of pragmatic trials.

OCHIN Epic includes a robust suite of tools designed to support collecting and acting on social risk data, many developed through NIH-funded studies.(28, 49–54) One such tool, CR, was made available to OCHIN members in 2022. CR is an integrated EHR tool that supports comprehensive care coordination for high-touch care management, including assessing patients’ social needs, making referrals to community organizations, and tracking referral outcomes to ascertain receipt of community services. Yet at present, an estimated < 10% of health centers use these functionalities to make referrals and track referral outcomes.

All OCHIN health centers that have activated the CR tools in their EHR and participate in one or more CM, population health, or value-based payment model programs that require care coordination of social needs for patients will be eligible for the trial. Such programs include CMS’s care management programs, CalAIM, and patient-centered medical home (PCMH) programs. At least 42 OCHIN member health centers met these criteria at study start-up (November 2023) and another six had adopted CR tools by March 2024. We anticipate that even more health centers do so and thus be eligible for recruitment in early 2025.

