### Data

All quantitative data will be extracted from the OCHIN EHR, including clinical-community care coordination activities performed by care management / population health providers using CR, and patients’ demographic, medical, laboratory, and social risk data.(70, 71) Qualitative data will come from periodic reflections and interviews with CM staff. Using similar methods as applied in formative activities, periodic reflections will be conducted at intervention period weeks 4 and 8. Semi-structured interviews with one key informant (e.g. care manager, health center champion) per health center will be conducted three to six months post intervention.

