**OUTER CONTEXT**		

Accreditation/regulation	EHR application targeted by intervention	Reimbursement of social needs screening, referral and community organization linkage are important components of CM and emerging value-based care programs

Economic environment	Outcome	Clinics will need to demonstrate their ability to support clinical-community linkages to be competitive for emerging value-based care contracts

Facilitators	Intervention	Broad health center partner engagement will inform implementation strategies that will comprise the intervention to improve clinical-community linkages

Vendor	EHR application/tools targeted by intervention	Epic is an EHR vendor and tool developer that supports the operationalization of clinical-community linkages

**Table 2 T2:** Role of formative activities on refining implementation strategies

Implementation strategy	*Formative activities will provide needed input in the following areas to refine the intervention for live testing in health centers*:		
	Content	Format	Cadence
**Dedicated training** to foster adoption and efficient use of enabling technologies to support social needs care coordination activities(34)	- Topics to cover at initial training - Ongoing training content	- Individual or group - Synchronous, asynchronous or hybrid	- Length of initial training - Frequency of booster trainings
**Clinic champions** promote buy-in and engagement by building internal support and mobilizing resources(87)	- Recruitment criteria for champion - Scope of champion role	- On-site assessment of adoption by users - Communication preferences with study team	- Hours per week needed to accomplish champion activities
**Practice coaches** facilitate workflow redesign to optimize adoption of enabling technologies(88)	- Focus within one department or across departments - Coordinate with ongoing internal and external initiatives to screen, refer, and ascertain receipt of services	- Individual or group - Synchronous, asynchronous or hybrid	- Hours of initial practice coaching support needed by health center - Frequency of meetings through implementation
**Audit & feedback** reports show progress and evidence needed to facilitate benchmarking and motivate users(89)	- Determine data to display to show progress and adoption of enabling technologies and receipt of community services (closed-loop referrals)	- Use of graphs, tables, and text to convey information	- Frequency of report creation, distribution, and review

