**Table 3 T3:** Stepped-wedge design

					Year 1	Year 2		Year 3				Year 4				Year 5			
Q1	Q2	Q3	Q4	Q1	Q2	Q3	Q4	Q1	Q2	Q3	Q4	Q1	Q2	Q3	Q4	Q1	Q2	Q3	Q4
Wedge 1 (Health Centers 1–4)					Formative Intervention Refinement	C	C	I	F	F	F	F	F	F	Analysis and Dissemination				
Wedge 2 (Health Centers 5–8)						C	C	C	I	F	F	F	F	F					
Wedge 3 (Health Centers 9–12)						C	C	C	C	I	F	F	F	F					
Wedge 4 (Health Centers 13–16)						C	C	C	C	C	I	F	F	F					
Wedge 5 (Health Centers 17–20)						C	C	C	C	C	C	I	F	F					

Note: C = Control condition, I = Intervention condition, F = Follow-up.

**Table 4 T4:** Outcomes Per RE-AIM Framework.

RE-AIM Outcome	Outcome Type	Measure
Reach	Primary	binary outcome of whether the patient has been screened for unmet social needs
Effectiveness	Primary Secondary Secondary	binary outcome of whether the patient with an unmet social need received a referral to a community organization to address an identified social need binary outcome of controlled hypertension binary outcome of controlled diabetes
Adoption	Secondary	binary outcome of receipt of community services (closed-loop referral) among patients with a social need who were referred to community organizations
Implementation	Secondary	*assessed through qualitative methods
Maintenance	Secondary	*assessed through qualitative methods

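### Recorded receipt of community services depends on referral tracking that the intervention promotes, so the closed-loop contrast mixes better recording with more services received

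*Protocol article*

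**What the plan says.** The Outcomes section lists as a secondary outcome "receipt of community services (closed-loop referral) among patients with unmet social needs who were referred to community organizations (binary". Table 4 repeats it almost word for word and places it in the Adoption row, not the Effectiveness row.

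The Setting section explains how receipt becomes known: Compass Rose supports "tracking referral outcomes to ascertain receipt of community services". It adds that "an estimated < 10% of health centers use these functionalities to make referrals and track referral outcomes". The Data section states that "All quantitative data will be extracted from the OCHIN EHR" and names no patient report or community-organization record as a further quantitative source.

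Table 2 lists what the formative phase is to settle for each strategy. For audit and feedback the content item is "Determine data to display to show progress and adoption of enabling technologies and receipt of community services (closed-loop referrals". For practice coaching, the content includes coordination with initiatives that ascertain whether services were received.

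The Background hypothesis is that the strategies "will improve the adoption of these technologies and thus social risk screening, community referrals, and receipt of services by patients with unmet social needs". The Analyses section restricts the closed-loop analysis to care-management patients who received a referral.

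**The concern.** A referred patient can be recorded as having received a service only if two things happen: the service was received, and someone at the center tracked the referral to its outcome. The intervention is meant to increase the use of the tool that does the tracking. Randomizing the order of the wedges does not protect against this, because the change in measurement is itself caused by the intervention and starts at the same point as any real effect.

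The article recognizes a similar problem elsewhere. The Analyses section says that centers vary widely in recording declined referrals and that implementation support will include guidance on recording them. The Outcomes section fixes a rule for patients with no A1c or blood pressure value. Neither the analysis text nor Limitations and Considerations raises the corresponding problem for receipt of services.

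At stake is one of the three consequences named in the study hypothesis. A rise in the recorded rate could be reported as more patients getting help when part or all of it is better documentation.

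**Working it through.** **The plan's own figures.** The article states power only for the referral outcome, above 80% for 48% versus 63.3% at ICC 0.15 and for 48% versus 72% at ICC 0.30. A stepped-wedge calculation on cluster-period means (20 centers, five sequences, six periods, both autocorrelations 0, two-sided 0.05) gives 0.82 to 0.89 and 0.92 to 0.96 for 27 to 163 patients per center-period. The stated power is therefore reproduced. It does not concern the closed-loop outcome, for which no figure is given.

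**Inputs for this point.** Let *r* be the true probability of receipt among referred patients and *t* the probability that a referral's outcome is tracked. The article gives neither, so both are assumptions. For simplicity *t* is taken to be the same whether or not the service was received.

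**Case A: untracked counts as not received.** Recorded receipt = *r* × *t*. Hold *r* at 40% in both conditions, so the intervention has no effect on services:

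| Tracking, control → intervention | Recorded receipt | Apparent gain | Odds ratio |
|---|---|---|---|
| 10% → 40% | 0.40×0.10 = 4% → 0.40×0.40 = 16% | 12 points | (0.16/0.84)/(0.04/0.96) = 4.6 |
| 30% → 60% | 0.40×0.30 = 12% → 0.40×0.60 = 24% | 12 points | (0.24/0.76)/(0.12/0.88) = 2.3 |
| 20% → 30% | 0.40×0.20 = 8% → 0.40×0.30 = 12% | 4 points | (0.12/0.88)/(0.08/0.92) = 1.6 |

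The apparent gain is *r* × (*t* under intervention − *t* under control), which is zero if tracking does not change. With *r* varied from 20% to 70%, the apparent odds ratio is 3.1 to 3.5 for tracking 10% → 30%, 5.4 to 7.2 for 10% → 50%, and 1.5 to 1.6 for 20% → 30%.

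The same power calculation shows how often such an artefact would be significant, with 163 × 0.48 = 78 referred patients per center-period and tracking 10% → 30%. At *r* = 50% the chance is 92% at ICC 0.15 and above 99% at ICC 0.05. At *r* = 20% it is 53% and 91%.

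**Case B: untracked is excluded.** Write *a* for the tracking probability among patients who received the service and *b* for that among those who did not. The observed rate among tracked referrals is *ra* / (*ra* + (1 − *r*)*b*). It equals *r* only if *a* = *b*. If the intervention changes the ratio of *a* to *b*, the observed rate moves even though *r* does not, and the article gives no basis for saying which way.

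**What bounds would show.** True receipt lies between *rt* (no untracked patient received the service) and *rt* + (1 − *t*) (all did). In the first row this is 4% to 94% in control (4 + 90) and 16% to 76% under intervention (16 + 60). In the second it is 12% to 82% (12 + 70) and 24% to 64% (24 + 40). The intervals overlap almost entirely, so these data alone could not settle whether receipt differed.

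**The case against.** The strongest reply has four parts.

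- **Coding of untracked referrals.** The article does not say that an untracked referral is scored as not received, and an analysis plan that is not shown may set the rule. This stands, and the missing rule is not the point made here. The point survives because neither obvious rule removes the problem: one adds an artefact and the other adds selection.
- **The < 10% figure.** A reader might infer from it that fewer than 2 of the 20 centers would track outcomes in control periods, so that most negatives there are unobserved. The article does not support that. The figure is a share of health centers, covers making referrals and tracking them together, and is not specific to trial centers, which must already use the tool. The analysis is also limited to patients with a referral. Tracking among referred patients at baseline is simply not given and could be well above 10%.
- **The Adoption label.** Placing documented closure under Adoption in Table 4 is defensible, and the article itself glosses the outcome as a closed-loop referral. What remains is that the outcome's name and the Background hypothesis treat it as services received by patients.
- **Intervention content.** Table 2 lists matters for formative input, so the final feedback and coaching content was not settled. The planned direction is nevertheless clear.

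**Conclusion.** The point holds as a limit on what the contrast can show. Receipt is visible only through tracking, tracking is a planned target of the intervention, and the article still words the result as receipt of services. A reader might go further and say that the contrast measures tracking rather than services. That is too strong: it reflects both, in unknown proportion, and a real increase in receipt may be part of it.

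The sizes shown (12 points at 40% true receipt for tracking 10% → 40% or 30% → 60%, 4 points for 20% → 30%) rest on assumed rates and on counting untracked referrals as not received. If tracking among referred patients is already high, or changes little, the artefact is small. This is a secondary outcome, but one named in the study hypothesis, so the wording should be changed before results are reported.

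**What to change.** 1. Rename the outcome documented loop closure in the Outcomes section and in Table 4, and keep it in the Adoption row.
2. Add the share of referred patients with any recorded referral outcome, compared by condition. This shows directly how far ascertainment changed.
3. Report receipt of services descriptively, with best-case and worst-case bounds for untracked referrals. Do not present it as an Effectiveness contrast restricted to tracked referrals, because that restriction conditions on something the intervention changes.
4. State, next to the Background hypothesis and in the limitations, that a between-condition difference in documented closure is not by itself evidence that more patients received services.

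The cost is a weaker claim about receipt, some rewording and a small amount of extra tabulation. This assumes that the EHR extract can separate a referral with no outcome recorded from one recorded as not received. The article does not describe those fields, so this should be checked first.

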### Main Trial Study Design

Following the formative intervention development described above, a stepped-wedge cluster randomized trial (SW-CRT) will be conducted across 20 OCHIN member health centers, with health centers serving as the clusters. A CONSORT flow diagram outlining the randomization and intervention allocation is provided in Fig. 2.(65) In this trial, the CM teams within each health center will undergo a 12-week implementation support intervention. The stepped-wedge design enables the phased delivery of the intervention to small groups of health centers (four per wedge; five wedges). This approach optimizes study resources while maintaining methodological rigor, leveraging the higher statistical power in this design compared to other CRT designs.(50, 66–68) It also ensures that all participating health centers eventually receive the intervention, potentially enhancing study recruitment.

The 20 recruited health centers will be randomly assigned to one of five wedges using a random number generator independently by the study’s statistician with SAS software for staggered receipt of the intervention. The statistician will have no direct interaction with the health centers and will not be involved in the recruitment of these health centers into the study. Recruitment efforts will be led by the study’s Project Manager and Project Director. These health centers will initially start in the control condition, with each wedge sequentially transitioning (per randomization) to the intervention condition every three months. This process continues until all health centers receive the full 12-week intervention (Table 3). Before receiving the intervention, all study health centers will contribute at least six months of baseline data. After receiving the intervention, all study health centers will continue to be followed until the end of the main trial period, which will span from approximately January 2025 (start of baseline data collection) to June 2027 (end of follow-up for all wedges). The intervention will be delivered to health centers from July 2025 to September 2026. The final wedge to receive the implementation support will be followed for six months in the intervention condition. Participating health centers will receive an impact payment for their involvement.

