### Analyses

Primary outcomes will be measured at six time points for each health center: at baseline and at the end of each of the five wedge’s receipt of the intervention during the CRT. At each time point, all active CM patients receiving care management in a CR program that incorporates social risk activities (e.g. CalAIM, CCM) will be included. The analyses use an open cohort design, as some patients will be measured across multiple time points and others only once. We will identify whether each eligible patient has been screened. We will also identify if patients who screened positive for a social need were referred to a community organization; to the extent possible we will also identify which patients with social needs declined offered referrals. Currently, there is large variability in whether health centers collect data on patients who decline referrals. We will guide on collecting this information as part of implementation support, and we will investigate if we can assess declined referrals as part of our analyses. As the main outcomes are binary and patients are nested in health centers, we will use generalized linear mixed models with a binomial distribution and a logit link and include a random effect for the health center. Patient-level covariates will include age, race/ethnicity, gender, federal poverty level, insurance type, care management program (e.g. CCM; CalAIM), and a health center-level indicator of treatment arm (intervention or control) for each time point.

The analysis for closed-loop referral (secondary outcome) will be limited to patients enrolled in CM that received a referral to a community organization for a social need. Clinical outcomes of hypertension and diabetes control will be limited to enrolled patients with hypertension and/or diabetes, respectively, and a medical visit during the measurement period.

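### Tying A1c control to the last visit makes the diabetes outcome a mix of glycaemic control and test timing; it should use the latest value in a stated period

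*Protocol article*

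**What the plan says.** The Outcomes section of the protocol article names two secondary clinical outcomes: "clinical outcomes such as controlled hypertension (among patients with diagnosed hypertension) and controlled diabetes (among patients with diagnosed diabetes"). Table 4 lists both under Effectiveness. Each is tied to one visit: "Controlled hypertension is defined as having a blood pressure < 140/90 mmHg at their most recent visit" and "Controlled diabetes is defined as having hemoglobin A1c ≤ 9.0 percent at their most recent visit". The same section adds a missing-value rule, with a cited source: patients with either diagnosis "who had a visit but no hemoglobin A1c measurement or blood pressure measurement will be considered to have “uncontrolled” disease".

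The Analyses section sets the denominator. The clinical outcomes are "limited to enrolled patients with hypertension and/or diabetes, respectively, and a medical visit during the measurement period". Patients with no such visit are left out and are not counted as failures.

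Timing is given only for other purposes. The sentence that sets six measurement occasions, the last five falling as each wedge completes its support, speaks of the primary outcomes: "Primary outcomes will be measured at six time points for each health center: at baseline and at the end of each of the five wedge’s". Main Trial Study Design gives the step length, "with each wedge sequentially transitioning (per randomization) to the intervention condition every three months". No measurement period and no A1c look-back are stated for the clinical outcomes.

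**The concern.** A1c is a laboratory test done at intervals, while visits happen for many reasons. Take a diabetic patient with an A1c of 7.0% early in the measurement period who comes back later in the same period for a medical visit without a blood draw. On the literal rule the last visit has no A1c, so the patient is recorded as uncontrolled although a qualifying result is in the record.

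Recorded control therefore depends on two things: whether the patient is controlled, and whether the last visit happened to carry a test. With testing held fixed, more visits lower recorded control. With visits held fixed, more testing raises it. Neither needs any change in glycaemia.

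Two consequences follow. A real improvement is diluted, because only patients tested at the last visit can show it. And if contact or testing shifts when a center crosses over, the comparison of conditions picks up that shift. None of the covariates listed under Analyses captures visit or testing frequency. In a hybrid type 2 trial, the two disease outcomes are where a reader will look for patient-level benefit.

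**Working it through.** **What the documents supply.** They give the two definitions, the missing-value rule, the denominator and the three-month step. They give no control rate, testing rate, visit rate or power statement for the clinical outcomes, so there is no stated figure to reproduce. Every rate below is an assumption, shown as a range.

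**Model.** Let c be true control and m the probability that the last visit carries a reading, with testing assumed unrelated to control. Under the literal rule, recorded control = c × m.

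**1. Number of visits.** Take c = 0.70 and one A1c per measurement period, drawn at a random one of k visits. Then m = 1/k.

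| Visits k | Last-visit rule, 0.70/k | Latest value in the period |
|---|---|---|
| 1 | 70% | 70% |
| 2 | 35% | 70% |
| 3 | 23% | 70% |
| 4 | 17.5% | 70% |

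Control and the number of tests are the same in every row. Only the number of visits changes.

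**2. Dilution.** A true gain of 5 points is recorded as 5 × m.
- m = 0.30: 1.5 points
- m = 0.50: 2.5 points
- m = 0.95 (a possible value for blood pressure): 4.75 points

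**3. Spurious difference if m shifts.** With c unchanged, the recorded difference is c × (m₁ − m₀).

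| c | m 0.30 to 0.40 | m 0.50 to 0.60 | m 0.95 to 0.97 |
|---|---|---|---|
| 0.60 | 18% to 24%, OR 1.44 | 30% to 36%, OR 1.31 | 57.0% to 58.2%, OR 1.05 |
| 0.70 | 21% to 28%, OR 1.46 | 35% to 42%, OR 1.34 | 66.5% to 67.9%, OR 1.07 |
| 0.80 | 24% to 32%, OR 1.49 | 40% to 48%, OR 1.38 | 76.0% to 77.6%, OR 1.09 |

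The first two columns are plausible for A1c and give 6 to 8 points. The last is plausible for blood pressure and gives 1.2 to 1.6 points.

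**4. How much of the outcome is measurement.** The share of outcome variance due to having a reading is c²m(1 − m) / [cm(1 − cm)], which simplifies to c(1 − m)/(1 − cm).
- Lowest A1c case, c = 0.60 and m = 0.50: 0.30/0.70 = 43%.
- Highest A1c case, c = 0.80 and m = 0.30: 0.56/0.76 = 74%.
- Blood pressure, m = 0.95: 0.03/0.43 = 7% at c = 0.60, up to 0.04/0.24 = 17% at c = 0.80.

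**5. Dependence on the window.** If the latest value in the period is used and missing stays uncontrolled, recorded control is c times the share with any value in the period. With c = 0.70 and two evenly spaced tests a year, a three-month window catches half the patients (0.70 × 0.50 = 35%). A six-month window catches all of them (70%). The period length must therefore be stated.

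**The case against.** **The text has a milder reading.** The missing-value sentence does not say that the measurement must be absent at the last visit. Read with the denominator in Analyses, it could mean none in the whole period. The patient with an earlier A1c would then fall outside the missing-value rule. This stands as a possible reading, but it does not settle the matter: the definition of control still asks for a value at the last visit, so that patient meets neither rule clearly. Two programmers could extract different outcomes from the same text.

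**The outcome is not a pure testing measure.** A reader might infer that it tracks testing and visits instead of disease control. It does not: nobody counts as controlled without a qualifying value. It is a composite.

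**A shift at crossover is not shown.** The intervention consists of training, champions, practice coaching and audit and feedback on social-need screening and referral. Nothing says that it targets A1c ordering or medical visits. A reader might infer that false effects are to be expected, but the documents support only that they are possible. If measurement does not shift, the rule only dilutes.

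**Blood pressure is a weak case.** If it is recorded at nearly every visit, the effect is small.

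**Missing-as-uncontrolled is a deliberate rule.** It is prespecified and cited. A reader might infer that it should give way to a main analysis of measured patients only. That would condition on testing after randomization and could itself introduce selection bias if testing changes. The rule can stay.

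**These are secondary outcomes.** The primary outcomes and the power statement are untouched.

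**Conclusion.** The point holds for A1c and is minor for blood pressure. As written, the diabetes outcome mixes control with whether the last visit carried a test, and the text does not say whether a missing measurement means none at that visit or none in the period.

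Dilution follows from the literal rule whenever some last visits have no A1c: to between 30% and 50% of the true effect if m is 0.30 to 0.50. A spurious effect of 6 to 8 points needs a further assumption, a 10-point change in m at crossover, which is possible but not shown. All of these sizes rest on assumed rates and on testing being unrelated to control. They do not rest on a quarterly window, and a reader should not infer one from the three-month step, because the documents state no measurement period for these outcomes.

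**What to change.** 1. State the measurement period for the clinical outcomes, and define both on the most recent A1c or blood pressure recorded within it, with the thresholds unchanged.
2. Apply the missing-as-uncontrolled rule only to patients with no value in that period, and say so.
3. Report the proportion of patients with a value, by condition and period, so that any shift in testing is visible.
4. Add a sensitivity analysis restricted to measured patients, or with imputation, beside the main result.

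The cost is a small change to wording and to the extraction logic. The Data section already says "All quantitative data will be extracted from the OCHIN EHR", and laboratory data are among them. One trade-off needs a decision: a short period leaves more patients without an A1c, while a period longer than the three-month step lets values from before crossover count in the intervention condition.
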